#### 6.9. Prior Treatment and Concomitant Therapy

##### 6.9.1. Prior Treatment

If, prior to participation in this trial, the subject has received any of the following treatments for the current sub-macular hemorrhage, the date of treatment, details of the treatment (product name and/or type of gas), and dose shall be recorded in the case report form.

- i. Intravitreal administration of a tPA product.
- ii. Intravitreal gas injection.

##### 6.9.2. Concomitant Medication / Concomitant Therapy

###### 6.9.2.1. Prohibited Medications / Prohibited Therapies

The following are prohibited during the study period:

- 1) Defibrinated sodium (Defaterio).
- 2) Intravenous, sub-retinal, or intravitreal administration of tPA products other than alteplase (recombinant).
- 3) Intravenous or intravitreal administration of alteplase (recombinant).
- 4) Ophthalmic surgeries not listed in 6.9.2.2.

###### 6.9.2.2. Permitted Medications / Permitted Therapies

The following surgical treatments or drug uses are permitted:

- 1) Phacoemulsification cataract extraction and intra-ocular lens implantation.
- 2) Epiretinal membrane and internal limiting membrane peeling.

- 3) Retinal photocoagulation or cryotherapy for retinal tears.
- 4) Antiplatelet agents (including agents with platelet-aggregation-inhibiting activity) and anticoagulants.

#### 7. Discontinuation of Trial Intervention and Subject Discontinuation/Withdrawal

This section describes discontinuation for individual subjects; discontinuation of the trial at a trial site or termination of the entire trial is described in Appendix 1.

##### 7.1. Discontinuation of Trial Intervention

If, prior to surgery, the principal investigator or sub-investigator determines that the subject's systemic condition has deteriorated such that sub-retinal administration of montepase (recombinant) cannot be performed, the trial intervention shall be discontinued.

##### 7.2. Subject Discontinuation/Withdrawal

The trial for a subject shall be discontinued if any of the following applies:

- 1) The subject withdraws consent (the detailed reason for withdrawal shall be recorded in the case report form).
- 2) The subject is found to be ineligible after enrollment.
- 3) Based on a comprehensive safety assessment, including the occurrence of adverse events, the principal investigator or sub-investigator judges that continuation of the trial is infeasible (the detailed reason for infeasibility shall be recorded in the case report form).
- 4) The subject dies.
- 5) After trial initiation it becomes evident that, due to the subject's circumstances, required subsequent examinations or observations cannot be performed.
- 6) The subject meets the definition of loss to follow-up as defined in Section 7.3.
- 7) Any other situation in which the principal investigator or sub-investigator judges continuation of the trial to be infeasible (the detailed reason for trial discontinuation shall be recorded in the case report form).

At the time of discontinuation, appropriate medical care shall be provided based on the physician's judgment. To the extent feasible, the observations and examinations specified in the protocol for trial discontinuation shall be performed to evaluate safety. If the trial is discontinued because of an adverse event, the event shall be classified according to Section 10.2.3 (outcome categories 1, 4, 5) and follow-up of the adverse event shall be conducted up to 28 days after discontinuation. If follow-up cannot be performed, the reason shall be documented in the case report form. No discontinuation assessments shall be performed

for discontinuations that occur prior to any trial intervention.

A subject may withdraw from the trial at any time, for any reason or without providing a reason, upon the subject's own request, and no disadvantage shall result. Even if a subject withdraws consent, data collected prior to withdrawal shall, in principle, be included in the analysis set.

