#### 8.4. Adverse Events, Serious Adverse Events, and Other Safety Reporting

The definitions of adverse event (AE) and serious adverse event (SAE) are provided in

Appendices 2-10.2.1 and 10.2.2. The principal investigator or sub-investigator is responsible for the identification, documentation, and reporting of any event that meets the definitions of AE or SAE. They are also responsible for the follow-up of all adverse events (see Section 7.2). This includes events reported on the subject. The procedures for recording, assessing, determining causality of AEs or SAEs, and for preparing and transmitting SAE reports are described in Appendix 2-10.2.3.

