#### 8.4.3. Follow-up of Adverse Events and Serious Adverse Events

After the initial AE/SAE report, the principal investigator or sub-investigator shall actively follow each subject at subsequent visits or contacts. All AEs shall be followed until the event resolves, the condition stabilizes, it becomes evident that the event was caused by another factor, or the subject becomes lost to follow-up (as defined in 7.3). Details of the follow-up procedures are provided in Appendix 2-10.2.3.

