In certain situations, when an SAE occurs, the principal investigator may not have obtained all information required for the initial report to the trial coordinator. Nevertheless, the principal investigator must conduct a causality assessment for each event before transmitting the SAE

data to the trial coordinator as the first report. The principal investigator or sub-investigator may revise the causality opinion in light of additional information, amend the causality assessment accordingly, and prepare an updated SAE follow-up report.

<Outcome>

The outcome of an adverse event shall be classified into one of the following categories.

- 1) Recovered: The adverse event has resolved, and the subject has returned to the pre-onset condition.
- 2) Improving: The adverse event has almost resolved, and the subject has returned to a condition close to that before onset.
- 3) Not recovered: The adverse event has not resolved, and the subject remains in the same condition as at the time of onset (unchanged).
- 4) Recovered with sequelae: The adverse event has resolved, but the subject has residual sequelae.
- 5) Death: The subject has died (regardless of causality).
- 6) Unknown: Outcome is unknown due to lack of information.

<Follow-up of Adverse Events and Serious Adverse Events>

The principal investigator or sub-investigator shall, when medically necessary or upon request from the trial coordinating physician, conduct or arrange additional examinations and/or assessments as needed to elucidate, to the greatest extent possible, the nature and/or causality of an AE or SAE. Such additional examinations may include clinical laboratory tests, ophthalmologic examinations, or consultations with other healthcare specialists.

Even if the subject does not return to normal or to the pre-investigational-product level, the principal investigator or sub-investigator may discontinue follow-up for that subject if, based on the follow-up findings, they determine that further follow-up is unnecessary and that such a decision is justified from the perspective of subject protection.

The principal investigator or sub-investigator shall document the information related to the follow-up.

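### Section 7.2 discontinues subjects found ineligible even after dosing, which ends only the observation of treated subjects whom the FAS keeps; its 28-day adverse-event sentence also needs reconciling with 8.4.3 and 10.2.3

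*Protocol*

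**What the plan says.** **Ineligibility.** Section 7.2 opens its list with "The trial for a subject shall be discontinued if any of the following applies", and item 2 of the list is "The subject is found to be ineligible after enrollment". The item has no time limit. The section waives the discontinuation examination only "for discontinuations that occur prior to any trial intervention", so the list as a whole also covers subjects who have been operated on.

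**What is left to stop.** Table 6-1 gives monteplase once. Section 6.6 rules out further sub-retinal doses after Visit 1 except for re-bleeding. Section 7.1 deals with stopping the intervention itself, and only before surgery.

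**Who is analysed.** Section 9.2 removes a dosed subject from the FAS only if there are no post-dose efficacy data or there was a serious GCP violation. Under 6.3, a registration is not cancelled unless the subject withdraws consent and refuses data use.

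**Adverse events.** When an adverse event causes discontinuation, 7.2 says "follow-up of the adverse event shall be conducted up to 28 days after discontinuation" and names outcome categories 1, 4 and 5 only. Section 8.4.3 says "All AEs shall be followed until the event resolves, the condition stabilizes, it becomes evident that the event was caused by another factor"; loss to follow-up is its only other end point. Section 8.4 sends the reader to 7.2 for follow-up of all adverse events. Section 10.2.3 lists six outcome categories and lets investigators end follow-up when "they determine that further follow-up is unnecessary and that such a decision is justified from the perspective of subject protection".

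**The concern.** A rule that takes ineligible subjects out of a trial makes sense while treatment can still be withheld. Visit 1 may fall up to 7 days after registration, so criterion 2 has a real use in that interval. After the operation it withholds nothing on the schedule. It only ends the visits that would show what happened to a treated eye.

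The decision is also not fully objective. Exclusion criteria 1, 3 and 15 in 5.2 rest on the investigator's judgement, and there is no masking (6.4). Screening may be done at a partner site, with results viewed by web camera and the signed copy, on which monitoring is done, sent later by post (Appendix 4). A problem with eligibility can therefore come to light after surgery, when the early result is already known. Removal at that point could depend on outcome, in a trial of 20 subjects with no comparison group.

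The adverse-event sentence raises a different question. A site with a subject discontinued because of an adverse event finds three rules on how long to follow that event, and they do not agree.

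**Working it through.** **1. Which endpoints the rule can remove.** Visit windows come from the Schedule of Activities (1.3). I assume that the +7-day discontinuation window runs from the day of discontinuation, D, so the examination falls between Day D and Day D + 7.

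| Endpoint visit | Window | Earliest D whose examination can reach the window |
|---|---|---|
| Week 1 (Day 8, −1 to +3) | Days 7 to 11 | Day 1 (1 + 7 = 8) |
| Week 4 (Day 29, ±3) | Days 26 to 32 | Day 19 (19 + 7 = 26) |
| Week 12 (Day 85, ±7) | Days 78 to 92 | Day 71 (71 + 7 = 78) |

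- A dosed subject discontinued before Day 19 cannot supply a Week 4 value, and one discontinued before Day 71 cannot supply a Week 12 value, even with the discontinuation visit.
- Week 1 is less exposed. A subject found ineligible after the Week 1 visit keeps the primary value. One found ineligible earlier may still have a discontinuation OCT in Days 7 to 11, but need not: with D = 3 the examination may fall on any of Days 3 to 10, and 7.2 asks for it only where feasible. Section 3 chose Week 1 as a time when gas no longer interferes with OCT, so an earlier OCT may not be usable.

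**2. The plan's own sample size.** Inputs from 9.9: d = 0.70 (mean change −120 µm, SD 170 µm), two-sided α = 0.05, power 80%, dropout 5%. For a one-sample t-test with non-centrality d√n and critical value c = t(0.975, n − 1):

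Power = 1 − F(c; n − 1, d√n) + F(−c; n − 1, d√n), where F is the noncentral-t distribution function.

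At d = 0.70 the smallest n with at least 80% power is 19, and 19 / 0.95 = 20. Both stated figures are reproduced, and the allowance is exactly one subject.

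**3. Scale if Week 1 values are missing (d = 0.70).**

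| Evaluable n | Power |
|---|---|
| 20 | 0.8435 |
| 19 | 0.8225 |
| 18 | 0.7992 |
| 17 | 0.7733 |
| 16 | 0.7445 |

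With the unrounded d = 120/170 = 0.7059, n = 18 gives 0.8057. Whether a second missing subject takes power below 80% therefore depends on rounding of d.

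**4. Adverse-event follow-up, side by side.**

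| Section | Applies to | End of follow-up |
|---|---|---|
| 7.2 | Events causing discontinuation | 28 days after discontinuation; categories 1, 4, 5 |
| 8.4.3 | All events | Resolution, stabilization, another cause, or loss to follow-up; no time limit |
| 10.2.3 | All events | May end earlier on investigator judgement; categories 1 to 6 |

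An event that is improving, unchanged or of unknown outcome at 28 days falls in category 2, 3 or 6, none of which 7.2 names.

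**The case against.** The strongest case on the other side is that little is lost.

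- **A discontinuation visit exists.** The schedule marks OCT, visual acuity, pressure and fundus examination for it, and earlier data stay in the analysis. This stands. A reader might infer that treated subjects drop out of the primary analysis, or that their efficacy and safety data are lost altogether. The protocol does not support that: the FAS does not exclude on ineligibility, the safety set is all dosed subjects, and Week 1 is exposed only in the short interval after dosing.
- **Adverse-event collection is not shown to stop.** Section 8.4.1 runs it from dosing to the end of the observation period and does not end it on discontinuation for ineligibility. This stands too.
- **Missing data belong to the SAP.** Section 9.1.4 assigns them there, so the absence of ineligibility from Table 3-1 is not itself an error. That is right, but an SAP cannot restore visits that the protocol told sites not to make.
- **Post-dose discovery should be rare.** Registration requires confirmed eligibility. This is plausible, and the protocol gives no rate either way. The power figures are therefore a scale and not a forecast.
- **The 28-day limit is easily over-read.** It concerns only discontinuations caused by adverse events and has no bearing on ineligibility. A reader might compare it with Day 85 and conclude that follow-up is cut short whenever such a discontinuation falls before Day 57 (85 − 28 = 57). But Day 85 ends the collection of events, whereas 8.4.3 sets no end date, and 10.2.3 allows an earlier stop for any event. It is therefore not established that these events get the shortest follow-up.

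What remains is that criterion 2 as written reaches treated subjects and ends observation that the analysis set could use.

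**Conclusion.** The point holds in this limited form. Criterion 2 of 7.2 applies after dosing, when it ends scheduled observation and no scheduled treatment, in subjects whom 9.2 does not exclude for ineligibility. The exposed endpoints are mainly Weeks 4 and 12. The primary endpoint is exposed only when ineligibility is found between dosing and the Week 1 visit and no usable OCT falls in the window.

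The size of the loss, and the direction of any bias, cannot be computed from the protocol. Each subject is 1/20 = 5% of the sample, the plan allows for one without a primary value, and a second takes power to about 79.9% at d = 0.70. No stated figure in 9.9 is wrong on this point.

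Two assumptions matter. The discontinuation window is counted from the day of discontinuation, and ineligibility alone is not treated as a serious GCP violation, a term 9.2 does not define.

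Separately, the adverse-event follow-up wording in 7.2, 8.4, 8.4.3 and 10.2.3 is inconsistent and must be reconciled. Nothing here says which follow-up rule is right.

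**What to change.** 1. In 7.2, limit criterion 2 to subjects found ineligible before the investigational product is given.
2. State that dosed subjects later found ineligible remain in the scheduled assessments to Week 12 and in the FAS, with the ineligibility recorded as a deviation. Say in 9.2 that ineligibility alone is not a serious GCP violation for this purpose.
3. Add one sensitivity analysis of the primary endpoint without these subjects.
4. Reconcile the 28-day and outcome-category sentence in 7.2 with 8.4.3 and 10.2.3, and correct the reference from 8.4 to match whatever is decided.

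The cost is a protocol amendment to wording and one extra analysis. The visits are already on the schedule, and the sample size does not change.

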### 7.3. Loss to Follow-up

A subject shall be considered lost to follow-up if the subject fails to attend scheduled visits and the trial site is unable to contact the subject.

If a subject does not attend a scheduled visit, the following actions shall be taken:

- 1) The trial site will contact the subject and reschedule the visit as soon as possible for any assessment date on which the subject did not attend the visit. Explain to the subject the importance of adhering to the instructed visit date, and confirm whether the subject wishes to continue participation in the trial and whether continuation is appropriate.
- 2) Before determining that a subject is lost to follow-up, the principal investigator, sub-investigator, or trial collaborator shall make every effort to contact the subject (by telephone or, if necessary, by sending certified mail to the last known address of the subject). The details of these actions shall be recorded in the subject's medical record.
- 3) If the inability to contact the subject persists, the subject shall be considered to have withdrawn from the trial.

## 8. Trial Assessments and Procedures

- ✓ The timing of trial evaluations is described in Section 1.3 Schedule. The procedures described in this section and the Schedule in Section 1.3 must be adhered to.
- ✓ Data obtained as part of routine clinical care and collected prior to obtaining informed consent for this trial may be used as screening or baseline data provided that they meet the criteria specified in the protocol and were performed within the time windows defined in the Schedule of Section 1.3.
- ✓ If a serious problem affecting trial continuation arises (e.g., a pandemic), alternative methods for subject visits, assessments, and monitoring may be implemented in accordance with regulatory authority and ethics committee requirements.
- ✓ For safety reasons or technical issues related to assessments, re-evaluation or off-schedule evaluations may be performed.

### 8.1. Screening (Baseline) Assessment Procedures

The procedures for ophthalmic examinations are described in 8.2 Efficacy Evaluation

## Procedures.

### 8.1.1. Subject Background

The following information shall be collected during the screening period.

- Date of informed consent
- Sex
- Age at the time of informed consent
- Date of diagnosis of AMD or RAM and treatment history
- Medical history (ocular diseases, and only those deemed clinically significant for this trial by the principal investigator or sub-investigator shall be recorded in the case report form)
- Comorbidities
- Presence or absence of drug allergy
- Prior treatment (if present, collect the information described in Section 6.9.1)

### 8.1.2. Height and Weight

Measure height and weight.

### 8.1.3. Chest X-ray

Obtain a frontal chest X-ray in the standing position. If standing is difficult, a seated position is acceptable. Record the presence or absence of abnormalities, and if present, document the findings in the case report form.

### 8.1.4. Electrocardiogram (ECG)

Perform a resting 12-lead electrocardiogram. Record the presence or absence of abnormalities, and if present, document the findings in the case report form.

## 8.2. Efficacy Assessment Procedures

### 8.2.1. Optical Coherence Tomography (OCT) (both eyes)

Using OCT under mydriasis, capture fundus images and measure CFT ( $\mu\text{m}$ ). Enter the measurement results and the instrument used in the case report form. When measurements are performed at the same medical institution, the same device shall be used throughout the clinical trial period, in principle.

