#### 1.3. Schedule of Activities (SoA)

| Activity                                     | Consent         | Screening             | Enrollment | Treatment period                 |                |                |                |                | Observation period |                 |                 |                 |                 | Discontinuation    |
|----------------------------------------------|-----------------|-----------------------------------|------------|----------------------------------|----------------|----------------|----------------|----------------|--------------------|-----------------|-----------------|-----------------|-----------------|--------------------------------|
| Visit                                        |                 |                                   |            | Visit 1                          | Visit 2        | Visit 3        | Visit 4        | Visit 5        | Visit 6            | Visit 7         | Visit 8         | Visit 9         | Visit 10        |                                |
| Week                                         |                 | Within 7 days before registration |            | 0                                |                |                |                | 1              | 2                  | 3               | 4               | 8               | 12              |                                |
| Day                                          |                 |                                   |            | 1                                | 2              | 3              | 4              | 8              | 15                 | 22              | 29              | 57              | 85              |                                |
| Visit window (Day)                           |                 |                                   |            | Within 7 days after registration | —              | —              | —              | -1~+3          | $\pm 3$            | $\pm 3$         | $\pm 3$         | $\pm 7$         | $\pm 7$         | +7                             |
| Intervention                                 |                 |                                   |            | ○                                |                |                |                |                |                    |                 |                 |                 |                 |                                |

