| Chest X-ray                                  |                 | ○                     |            |                                  |                |                |                |                |                    |                 |                 |                 |                 |                                |
| Electrocardiogram                            |                 | ○                     |            |                                  |                |                |                |                |                    |                 |                 |                 |                 |                                |
| Concomitant medications / therapies          |                 |                                   |            |                                  |                |                |                |                |                    |                 |                 |                 |                 |                                |
| Adverse events                               |                 |                                   |            |                                  |                |                |                |                |                    |                 |                 |                 |                 |                                |

\*1 If a partner medical institution is not available, the clinical trial site shall be visited.

\*2 Either the partner medical institution or the trial site may be used. When multiple test results are available within the period, the data closest to the enrollment date shall be used.

\*3 If data are available within 7 days after enrollment, they may be used even before consent acquisition.

\*4 Measured before and after dosing.

\*5 Performed only on the treated eye.

\*6 May be performed at the trial site or at the partner site. If performed at the partner site, the trial site will provide remote medical care.

\*7 Performed only if discontinuation occurs before Visit 3.

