#### 9.1. General Considerations

##### ● Baseline Definition

Baseline assessments or events are defined as assessments or events that occurred prior to the date and time of administration of the investigational product. When multiple valid assessments or events are available, the assessment closest to the investigational product administration date (and time, if collected) shall be used as the baseline for analysis.

- Summary Statistics

For continuous variables, summary statistics shall include the number of observations, mean, standard deviation, minimum, median, maximum, first quartile (25th percentile), and third quartile (75th percentile). For categorical variables, summary statistics shall include the number of observations and the frequency and percentage (%) of each category.

Means, standard deviations, medians, first quartiles, and third quartiles shall be rounded to two decimal places and displayed to one decimal place. Minimum and maximum values shall be rounded to one decimal place and displayed to the specified number of digits. Percentages (%) and the upper and lower limits of their confidence intervals shall be rounded to the second decimal place and displayed to one decimal place.

- Significance Level and Confidence Coefficient

Unless otherwise specified, the significance level for hypothesis testing shall be two-sided 5 %. For interval estimation, unless otherwise stated, two-sided intervals shall be used with a confidence coefficient of 95 %. P-values shall be rounded to the fourth decimal place and displayed to three decimal places; however, if the unrounded p-value is less than 0.001, it shall be uniformly reported as "<0.001".

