##### 9.3.1.1. Definition of the Endpoint

- Change: The change from baseline shall be calculated using the following formula.  
Change = measurement at week 1 – baseline value

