#### <Activities That May Be Performed When a Subject Visits a Partner Medical Institution>

- ✓ Explanation of the trial and obtaining informed consent
- ✓ Screening
- ✓ Assessments at Visit 6 (Week 2/Day 15), Visit 7 (Week 3/Day 22) and Visit 9 (Week 8/Day 57)
- ✓ Assessments at discontinuation
- ✓ Unscheduled visits (when deemed permissible by the principal investigator or sub-investigator)

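### For subjects screened at a partner site, nothing requires the baseline CFT scan to be on the OCT device used at Week 1, so a device difference can enter the primary change score

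*Protocol*

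**What the plan says.** **Endpoint.** Protocol 9.3.1.1 defines the primary variable as "Change = measurement at week 1 – baseline value". Section 9.1.1 tests its mean against zero in one arm.

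**Device.** Section 8.2.1 has the CFT value and the instrument recorded, and adds: "When measurements are performed at the same medical institution, the same device shall be used throughout the clinical trial period, in principle". The rule covers scans within one institution only. Section 10.4 requires partner sites to inspect their devices and manage their precision, but not to match or cross-calibrate them with the trial site.

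**Place.** The schedule in 1.3 allows screening at a partner site or at the trial site. Visit 5 (Week 1) lies in the trial-site hospitalization block, and Visits 8 and 10 (Weeks 4 and 12) are in-person trial-site visits. Among scheduled post-operative visits, 10.4 opens only these to partner sites: "Assessments at Visit 6 (Week 2/Day 15), Visit 7 (Week 3/Day 22) and Visit 9 (Week 8/Day 57".

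**Time.** The screening window is "Within 7 days before registration" and the surgery window is "Within 7 days after registration".

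**Choice of baseline scan.** Where several screening results exist, footnote *2 of the schedule says "the data closest to the enrollment date shall be used". Section 9.1 says "the assessment closest to the investigational product administration date (and time, if collected) shall be used as the baseline for analysis". Footnote *3 adds: "If data are available within 7 days after enrollment, they may be used even before consent acquisition".

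**The concern.** A change score in a single-arm trial is only as good as the comparability of its two measurements. A subject screened at a partner site has a baseline from one institution's OCT and a Week 1 value from another's. If the partner device reads systematically higher than the trial-site device, the reduction in CFT is overstated by that amount; if it reads lower, the reduction is understated. Any real change in CFT between the screening scan and surgery is likewise counted as part of the treatment effect. With no concurrent control, neither is subtracted out.

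Partner screening is an intended route. Section 2.3.2 calls the trial decentralized, and 10.1.7 provides remote consent for patients living far from the trial site. The planning mean and SD in 9.9, by contrast, come from a review at a single institution.

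This cannot be left to the analysis. An SAP can define how a recorded baseline is used, but it cannot supply a matched scan that was never taken.

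**Working it through.** **1. The plan's own figure.** Section 9.9 assumes an effect size of 0.7 (mean −120 µm, SD 170 µm), two-sided 5% and 80% power. A one-sample t-test with the noncentral t distribution gives power 0.799 at n = 18 and 0.823 at n = 19, so 19 subjects are needed; 19 / 0.95 = 20. The stated 19 and 20 reproduce, and nothing here changes them.

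**2. Age of the baseline.** 7 days (screening to registration) + 7 days (registration to surgery) = 14 days at most before surgery. This limit is the same for subjects screened at the trial site.

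**3. Who has unmatched scans.**

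| Screened at | Baseline OCT | Week 1 OCT | Same-device rule applies? |
|---|---|---|---|
| Trial site | trial site | trial site | yes, in principle |
| Partner site | partner site | trial site | no |

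The second row also holds for the Week 4 and Week 12 CFT changes.

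**4. When the two baseline rules differ.** If every OCT precedes enrollment, the scan closest to enrollment is also the last one before dosing, and both rules select it. They diverge only if a valid OCT falls between enrollment and dosing. None is scheduled at Visit 1, but section 8 allows off-schedule evaluations, so the case is possible.

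**5. What an offset would do.** The documents give no between-device difference, so the following is an assumed range. Let b be a common offset in a fraction f of subjects. The mean shift is m = f·b, the SD is √(170² + f(1−f)b²), and the noncentrality is √n × (mean / SD). At n = 19:

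| b (µm) | f | m (µm) | m / 120 | Rejection rate, true change 0 | Power, true change −120 µm, shift toward 0 |
|---|---|---|---|---|---|
| 10 | half | 5 | 4% | 5.2% | 80% |
| 20 | half | 10 | 8% | 5.7% | 76% |
| 40 | half | 20 | 17% | 7.7% | 67% |
| 60 | half | 30 | 25% | 11.1% | 58% |
| 10 | all | 10 | 8% | 5.7% | 76% |
| 20 | all | 20 | 17% | 7.8% | 68% |
| 40 | all | 40 | 33% | 16.3% | 49% |
| 60 | all | 60 | 50% | 30.8% | 31% |

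Without an offset the rejection rate is 5%, and power is 83% (mean 120, SD 170).

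**6. If offsets vary around zero instead.** A simulation with n = 20, 10 subjects screened at 5 or 10 partner sites, and independent site offsets with an assumed SD of 10–70 µm gives a rejection rate of about 5–6% with no true change and power of 81–85%. Extra random SD of 20, 40, 60 or 80 µm in all subjects gives power of 0.82, 0.81, 0.78 or 0.75 at n = 19. This is mainly noise, and it costs little.

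**The case against.** The strongest reply is that the documents show a route for bias but no amount. That stands. Neither the offset nor the partner-screened share is stated, two institutions may own the same model, and subjects screened at the trial site are covered by the device rule. A large inflation of the rejection rate needs a large offset of the same sign in most or all subjects, which nothing in the protocol supports; scattered offsets do little harm.

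Four stronger readings are tempting and should not be made.

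- *The baseline rules contradict each other outright.* Footnote *2 selects among screening results within the screening period, while 9.1 defines the analysis baseline. They give different answers only in the case set out in step 4.
- *The protocol concedes that CFT drifts before surgery.* The remarks in section 3 on reabsorption and re-bleeding concern long-term CFT change and explain the Week 4 and Week 12 time points. For this population, section 4.2 states that spontaneous resolution is unlikely. One may doubt that premise over 14 days, but the text does not establish drift.
- *Footnote *3 admits baseline OCT scans from after enrollment.* Its wording disagrees with the screening column, but the marker cannot be tied to the OCT row in the table as it can be read. Section 8 separately requires pre-consent data to fall within the schedule's windows. It may be a slip, with no shown effect on the primary endpoint.
- *Up to 24 days of uncontrolled change.* 7 + 7 + 7 + 3 = 24 days can separate the two scans, but that total stacks every extreme and includes up to 10 days after dosing. Only 14 are pre-surgical.

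It is also fair to say that the remedy is half available: section 8 permits an off-schedule scan, and 9.1 would then take it as baseline. What is missing is the requirement.

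**Conclusion.** The point holds in limited form. For partner-screened subjects the protocol lets the primary change score pair scans from different devices, the first up to 14 days before surgery. Any systematic device offset or pre-surgical change then passes into the mean one for one, weighted by the share of subjects affected. Size and direction are unknown. Under the assumed common offsets of 10–60 µm, the shift is 5–30 µm if half the subjects are affected and 10–60 µm if all are, in either direction; under offsets centered on zero, the effect is close to negligible.

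This does not invalidate the trial, the t-test or the sample size. It is a gap in an acquisition rule that should be closed because closing it is cheap and it cannot be repaired after the data are collected. The difference between footnote *2 and 9.1 is conditional and needs a clarifying sentence.

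**What to change.** - In 8.2.1 and 9.1, define baseline CFT for analysis as the last pre-dose OCT at the trial site, on the device to be used at Week 1, taken at admission before surgery. Add this scan to the schedule in 1.3. Keep partner-site OCT for eligibility.
- State that footnote *2 governs the selection of screening data and that 9.1 governs the analysis baseline. This matters more once the admission scan exists, because that scan falls between enrollment and dosing, exactly where the two rules diverge.
- Reconcile the wording of footnote *3 with the screening window.
- Add a sensitivity analysis of the primary endpoint restricted to same-device pairs, using the instrument already recorded under 8.2.1. It would also cover any subject without an admission scan.

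Cost: wording in 1.3, 8.2.1 and 9.1, and one repeat non-invasive OCT for each partner-screened subject at a hospitalization that already takes place. The clarifications and the sensitivity analysis need no new data, and the sample size is unchanged.
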